### 2.5. Data Management and Analysis Plan

All physical materials, such as answer sheets, hand-written responses to the tests, and informed consent originals, will be stored and safeguarded at Fe y Alegría headquarters in Guatemala. The data gathered from the assessments will be transcribed into computer files, which will be stored in secure online servers at Loyola Andalucía University and will only be accessed by authorized personnel from the research project. This data will be compiled and analyzed by the technicians and research assistants collecting the information, supervised by the senior members of the research team functioning as a steering group. Every participant will be assigned an identification number so their data can be compiled and analyzed anonymously, following the Organic Law on Personal Data Protection and Guarantee of Digital Rights 3/2018. If, at the time of data analysis, any potential risks to the participants’ mental health are found by the researchers, an unblinding procedure will take place to identify the participants and notify their school centre so they can take any actions deemed necessary with said children and their families. The funding body will undergo an auditing process in the middle and at the end of the study to ensure that the planned interventions are properly carried out.

Pre/post-evaluation data are best analyzed using an ANCOVA design in which post-scores are the dependent variable, and pre-scores serve as the covariate [63]. This will be conducted separately for each intervention, with the data collected at T2 serving as post-data for intervention 1 and pre-intervention baseline data for intervention 2. If desired, the effects of the two interventions can be directly compared by implementing a repeated measures ANCOVA. Given that it is likely that raw scores will be converted to and analyzed as percentile scores, normal distributions of the dependent variables may not be present. Accordingly, Bootstrapping or non-normal distributions in the Generalized Linear Framework should be considered to accommodate these data. Other covariates, such as sex, age, mean educational level of parents, etc., can be included in the analyses. It will also be possible to perform analyses for different subgroups of participants, either using multilevel, stratified models, or by separating out the subgroups, depending on the specific nature of the subgroups. In particular, we will explore the differences between the “normative” group (participants between the ages of 10 and 12, without any clinical diagnosis and with scores over the inclusion limit in the screening assessment tasks), and the “non-normative” group (participants 13 years old and above, having any clinical diagnosis, or with scores under the screening tasks limit). This last separation will be performed to explore the impact the program may have on children with additional difficulties. We will perform another ANCOVA analysis to explore the long-term changes in the participants at the end of the program (second block), considering the changes they might have experienced on the first block. Where multiple comparisons are undertaken due to the presence of many schools, age ranges, or other factors, appropriate corrections will be applied to the statistical tests. 

Since all children will receive the intervention, we want to explore the effects this program may have on the children who do not meet the inclusion criteria but usually have special educational needs. Due to the nature of the intervention, it is impossible to implement it in a manner that allows both participants and the personnel administering the intervention to participate blindly. However, the personnel from the research team assessing the data will be blinded to group assignment to ensure as much of an unbiased outcome as possible. The interpretation of the data will also have to consider the group assignment to conclude the efficacy of the program.

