## Abstract

Background: Guatemala remains one of the poorest countries in Central America and suffers from high rates of social inequality and violence. In addition to the negative impact that two years without attending school has had on Guatemalan children due to the consequences of the COVID-19 pandemic, this unfavourable socioeconomic context poses a risk to children’s emotional and cognitive development. This work presents a protocol for implementing a cognitive and emotional stimulation program aimed at increasing the academic performance of these children and consequently improving their quality of life. Methods: The protocol proposes the implementation of a randomized controlled trial to assess the efficacy of a 24-session-long stimulation program. It targets the cognitive functions of attention, language, executive functions, and social cognition, using the digital neurorehabilitation platform NeuronUP. The participants (*n* = 480) will be randomly assigned to an Experimental or Control group. Pre- and post-intervention assessments will be carried out, together with a follow-up in the next academic year, in which both groups will change roles. Results will be compared for the first and second years, looking for differences in academic and cognitive performance between groups. Discussion: Mid- and long-term outcomes are still unknown, but effective interventions based on this protocol are expected to facilitate the following benefits for participants: (1) improved cognitive and emotional development; (2) improved academic performance; (3) improved well-being. We expect to create a validated neuropsychological stimulation program that could be applied in similar socioeconomically disadvantaged contexts around the world to help these children improve their life chances.

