### 2.4. Procedure

The design of this study protocol follows the guidelines of the CONSORT-revised recommendations for improving the quality of reports of parallel group randomized trials [62]. The study has been pre-registered with the Open Science Foundation. Ideally, children should be randomly allocated to either the control or the experimental group. However, implementation of this protocol requires the use of at least two rooms at the same time, along with a high level of logistical organization in terms of moving the children to their correct rooms for each session. Given the nature of the schools involved, we do not believe it is realistic to expect that these resources will always be available. Hence, we propose that the study will be carried out through a multicentre randomized controlled trial in which entire classes of children will be assigned to either the control or experimental conditions. We note, however, that the members of each class are allocated at random by the school as they enroll, so in this sense, random allocation at the participant level is still somewhat achieved. To minimize potential bias related to school-specific factors, each school will provide [at least] two classes, thus ensuring that each school is represented in both conditions. Efforts should be made to ensure as close to a 1:1 ratio of students between groups as possible. The class designated as the experimental group will receive the intervention. The second group will be made up of the students who will form the control group. A crossover design will be used in which the role of each group is reversed during the following academic year, thus ensuring that each child has the opportunity to benefit from the intervention program. The study will therefore be divided into two blocks (see Figure 2). The first block will occur in year 1 and will consist of a prior and posterior assessment (T1 and T2) of the children’s cognitive and emotional abilities and the implementation of the intervention program in between. The second block will occur in year 2 and will consist of a second intervention, followed by a final assessment (T3), which will occur when the children are in the 6th grade. In this block, the control and experimental groups will change roles. Apart from ensuring that all children may benefit from the intervention program, it will provide an opportunity to determine if there is maintenance of the benefits obtained by the experimental group during the first block. All assessments will be carried out by professional neuropsychologists and educational psychologists, duly trained to administer the assessment tasks by the experts from the research team.

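### Whole classes are allocated, but the efficacy ANCOVA treats children as independent and has no class term, so its error rate exceeds 5% whenever classmates remain correlated after adjustment for the pre-score

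*Protocol article*

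**What the plan says.** Protocol article, section 2.4 (Procedure): after explaining that child-level allocation is not practical, the authors say that "entire classes of children will be assigned to either the control or experimental conditions". They add that schools form their classes at random at enrolment, and conclude that "random allocation at the participant level is still somewhat achieved". On schools: "each school will provide [at least] two classes, thus ensuring that each school is represented in both conditions". The Abstract says of the participants that they "will be randomly assigned to an Experimental or Control group".

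Section 2.5 (Data Management and Analysis Plan): "Pre/post-evaluation data are best analyzed using an ANCOVA design in which post-scores are the dependent variable, and pre-scores serve as the covariate". This is run separately for each of the two interventions. Four other statements bear on the model:

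- Covariates: "Other covariates, such as sex, age, mean educational level of parents, etc., can be included in the analyses". Class and school are not named.
- Multilevel models appear once, as an option for subgroup analyses: "either using multilevel, stratified models, or by separating out the subgroups".
- Schools appear once, under multiplicity: "Where multiple comparisons are undertaken due to the presence of many schools, age ranges, or other factors, appropriate corrections will be applied".
- Bootstrapping and generalized linear models are offered to deal with non-normal scores, not with clustering.

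Section 2.1.3 (Sample Size) says that the power calculation used this same analysis plan and gave a minimum of 352, with 480 to be recruited.

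**The concern.** When classes are allocated, the treatment contrast is a contrast between classes, and its error must include the variation between classes. An ANCOVA on individual children uses only the variation between children. Any class-wide influence on the post-score is then counted as many independent confirmations of a treatment effect.

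The article itself describes ways in which such influences can arise after baseline. Sessions are given to whole class groups by locally appointed staff (section 2.3.2). Part of the control activity is left to the responsible teaching staff (section 2.3.2). School access and internet connection are not guaranteed (section 2.4), so a disruption can hit a group together.

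The validity of the main test and its confidence interval is at stake, for both interventions. The programme is meant for school curricula and for transfer elsewhere (sections 3 and 4), so a false positive would be costly.

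**Working it through.** **Inputs from the article.** Five schools (section 2.1.2); at least two classes per school, so at least 10 classes (section 2.4); about 1,400 fifth-graders in these centres (section 2.1.2); d = 0.3, minimum n = 352, 480 recruited (section 2.1.3).

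**Assumptions.** Two-sided 5% and 80% power, which are not stated. A residual class ICC, that is, after pre-score adjustment, of 0.01 to 0.10. Three layouts:

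- 10 classes of 36: 480 × 0.75 = 360 completers, and 360/10 = 36.
- 20 classes of 24: all 480 children.
- 40 classes of 9: with full classes of 35, 1,400/35 = 40 classes; 480/40 = 12 recruited per class; 12 × 0.75 = 9 completers.

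**Step 1: the plan's own figure.** A two-sample t-test with d = 0.3 needs 176 children per arm, 352 in total (power 80.1%). The corresponding ANCOVA calculation (f = 0.15, one covariate) gives 351, with 80.1% power at 352. The stated figure is therefore reproduced with independent children and a design effect of 1.

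**Step 2: error rate of the child-level test.** With m children per class, DE = 1 + (m − 1) × ICC. The standard error is understated by a factor √DE, so the actual error is 2 × [1 − Φ(1.96/√DE)].

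Example, m = 36 and ICC = 0.05: DE = 1 + 35 × 0.05 = 2.75; 1.96/√2.75 = 1.18; error = 23.7%.

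| Residual ICC | 10 classes of 36: DE, error | 20 classes of 24: DE, error | 40 classes of 9: DE, error |
|---|---|---|---|
| 0.01 | 1.35, 9% | 1.23, 8% | 1.08, 6% |
| 0.02 | 1.70, 13% | 1.46, 10.5% | 1.16, 7% |
| 0.05 | 2.75, 24% | 2.15, 18% | 1.40, 10% |
| 0.10 | 4.50, 36% | 3.30, 28% | 1.80, 14% |

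**Step 3: simulation under no effect** (4,000 runs per setting, five schools, classes randomised within school). With 20 classes of 24, the child-level ANCOVA rejected in 5.2%, 7.6%, 10.1%, 18.1% and 28.8% of runs at ICC 0, 0.01, 0.02, 0.05 and 0.10. A class-mean analysis with school effects stayed between 4.3% and 5.6% in all settings run.

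**Step 4: is the school term to blame?** With school variance of 0.05 and no class variance, the child-level ANCOVA rejected in 3.7% to 5.1% of runs. Omitting school does not inflate the error. With class variance present, the inflation was about the same with or without school variance (for example 17.3% against 18.1% with 20 classes of 24 at ICC 0.05).

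**Step 5: power of a valid class-level test.** With K classes and five school effects, df = K − 6, and the noncentrality is 0.3/√(4 × DE/N), with d in residual SD units. For 10 classes of 36 at ICC 0.01: 0.3/√(4 × 1.35/360) = 2.45 against a critical t of 2.78 on 4 df, which gives 46%.

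| Residual ICC | 10 classes of 36 (4 df) | 40 classes of 9 (34 df) |
|---|---|---|
| 0.01 | 46% | 76% |
| 0.02 | 39% | 73% |
| 0.05 | 26% | 65% |
| 0.10 | 18% | 54% |

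**The case against.** The strongest reply has four parts.

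1. *Class rosters are random and the pre-score is a covariate.* Both reduce differences between classes that already exist at baseline, which is a good reason not to lean on the upper end of the ICC range. Neither removes correlation that arises between the two assessments in shared sessions. This limits the size but does not justify the child-level test.

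2. *The size cannot be read from the article.* This stands. A reader might infer that the false-positive rate is well above 5% in any case. The article does not support that: at ICC 0 there is no inflation, and with 40 classes of 9 at ICC 0.01 the rate is about 6%. Two classes per school is a minimum, and if about one child in three consents across all classes, many small class groups are plausible.

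3. *Schools are balanced across arms.* This also stands. A reader might blame the missing school term as well, but step 4 shows that it does not inflate the error. Adding school alone would not repair the test either.

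4. *This is a condensed article, the covariate list is open-ended, and multilevel models are mentioned.* A fuller plan, not at hand, might contain a class term. But the article does not merely leave the efficacy model open: it states one, argues that allocation is nearly individual, and rests the sample size on that plan. The multilevel option is confined to subgroups.

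The Abstract's wording can be read as shorthand that section 2.4 openly clarifies. It is a point of reporting and does not affect the standard error.

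**Conclusion.** The stated efficacy analysis does not fit the stated design. The class is the unit of allocation, the model has no class term, and its type I error exceeds 5% whenever the residual class ICC is above zero. Over residual ICCs of 0.01 to 0.10 the error runs from about 6% to 14% in the mildest layout and from 9% to 36% in the severest. These figures rest on assumed ICCs and class sizes and on a nominal two-sided 5% level. That the error is inflated follows from the design as soon as any residual correlation remains; how far cannot be fixed from the article. The cause is the missing class term alone. The main analysis should be corrected before efficacy is tested.

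**What to change.** For each efficacy comparison, regress the post-score on arm, pre-score and school, with a random intercept for class and small-sample degrees of freedom (Kenward-Roger or Satterthwaite). If there are only about 10 classes, use a school-stratified analysis of pre-score-adjusted class means instead. Any bootstrap or permutation must resample or re-randomise classes within school; resampling children keeps the flaw. Describe the trial as cluster-randomised, and align the Abstract and the participant-level sentence in section 2.4 with that.

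The cost is more than wording. Confidence intervals widen and power falls below what n = 352 implies: about 46% down to 18% with 10 classes of 36, and about 76% down to 54% with 40 classes of 9, over ICC 0.01 to 0.10. Section 2.1.3 should therefore restate its power basis with an assumed ICC, a number of classes and a class size. Using more classes per school with fewer participants in each, which section 2.4 already permits, limits the loss.

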#### 2.1.3. Sample Size

To ensure that the size of the improvements realized by the intervention are of practical significance, we propose a minimum effect size of Cohen’s *d* = 0.3, which is a small-to-medium effect. A power calculation using this effect size and the proposed analysis plan (see below) was carried out using the program G*Power [35] and indicated that the minimum sample size we require for the study is n = 352. However, due to the difficult living conditions in the proposed recruitment areas (gang violence, long distances from residences to school centres, etc.), we expect a high dropout rate. Therefore, we propose to recruit a total of 480 children as this would allow for slightly more than 25% of the sample to stop participation in the study yet still allow us to maintain sufficient statistical power to detect the target effect size. Furthermore, the figure of 480 represents approximately one-third of 5th grade students attending Fe y Alegría Guatemala across their 46 centres. Thus, we would only need consent from one in every three children to achieve the necessary sample size. This sample size could be reduced if research teams were prepared to look for larger effect sizes. Furthermore, once this protocol is implemented, research groups should consider creating a contingency plan based on the specific conditions they encounter to address potential difficulties in recruitment.

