
The program will take place during the second half of the academic year, at a rate of two sessions per week, with an estimated duration of about 45 min per session. Participants will complete the two weekly sessions on different days of the week, depending on the school they attend, but always with at least one rest day in between. If, for some reason, there are participants who miss one of the sessions, they would have to recover it during the same week to avoid the risk of falling behind their classmates. If participants miss a session and cannot recover it within the same week, they will skip that session and continue with the normal session planned for the following week, but the missed session will be registered as lost. The justification for this decision is that sometimes access to schools or a stable internet connection will not be guaranteed in the context of the study. Hence, this protocol will prevent participants from lagging behind their classmates and avoids having participants completing different sessions in the same classroom. An additional reason for making this decision is that at the end of the program, we will be able to analyze the percentage of completion for each participant and determine the minimum completion percentage to ensure the program’s effectiveness. 

One advantage of the group sessions is that many children can benefit from professional intervention without the need to have one therapist for each child. Nevertheless, children with a previously diagnosed condition are at risk of greater disadvantage compared to their counterparts and may need specialized, one-on-one attention. We do not propose that these children be excluded from the intervention. However, with the help Fe y Alegría, an alternative intervention will be offered to families that wish to receive additional support by referring them to specialized services offered for people with limited economical possibilities. Furthermore, teachers will be provided with training to effectively aid and support these students within the school. 

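### The block 2 ANCOVA adjusts T3 for T2, which block 1 treatment may already have shifted, so its estimate of intervention 2 is biased unless block 1 had no effect or its gains persist at exactly the T2–T3 slope

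*Protocol article*

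**What the plan says.** Section 2.4 describes two blocks. In year 1 the children are assessed at T1, one group receives the programme, and all are assessed again at T2. In year 2 the same class-allocated groups exchange roles and there is one further assessment, T3, after the second intervention. No new allocation and no new pre-assessment is described for year 2. Of this second block the section says that "it will provide an opportunity to determine if there is maintenance of the benefits obtained by the experimental group during the first block". On timing it says: "The program will take place during the second half of the academic year".

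Section 2.5 analyses each intervention by its own ANCOVA of post-score on pre-score, "with the data collected at T2 serving as post-data for intervention 1 and pre-intervention baseline data for intervention 2". It adds that, if wanted, "the effects of the two interventions can be directly compared by implementing a repeated measures ANCOVA". It also announces a further ANCOVA of long-term change at the end of block 2 that takes block 1 changes into account, without giving the model or covariate.

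Section 2.1.3 sets the size of effect: "we propose a minimum effect size of Cohen’s *d* = 0.3, which is a small-to-medium effect".

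**The concern.** In block 1 the ANCOVA is sound in principle, because T1 precedes treatment. In block 2 the covariate T2 follows it. If the programme works in year 1, the arms differ at T2 because of treatment. Adjusting for T2 then treats that difference as an ordinary baseline imbalance, expected to carry through to T3 at slope β. A treatment gain need not carry through at that rate: it may fade entirely or be kept in full. The mismatch goes straight into the estimate for intervention 2. A year 2 intervention that does nothing could appear to help or to harm, and one that works could be mis-sized.

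A second problem has a different cause. By T3 the comparison group has just had the programme, so no untreated group remains against which retention of the year 1 benefit could be judged.

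**Working it through.** **Inputs from the article.** The target effect is d = 0.3. The minimum analysed sample comes from the statement that the calculation "indicated that the minimum sample size we require for the study is n = 352". Recruitment is 480, of which the article says "this would allow for slightly more than 25% of the sample to stop participation in the study" (128/480 = 26.7%). Allocation is by class at about 1:1: "Efforts should be made to ensure as close to a 1:1 ratio of students between groups as possible".

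**Assumptions, not in the article.** Two-sided 5% test; 80% power; β from 0.5 to 0.8; r from 0 to 1; unit SD at each time point, so that β equals the within-arm T2–T3 correlation; equal correlation among T1, T2 and T3; independent children.

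**Step 1: the plan's own figure.** A two-sample t-test at d = 0.3, two-sided 0.05 and 80% power needs 176 per arm, or 352 in total, which matches. (The normal approximation gives 350; an ANCOVA F-test with f = 0.15 and one covariate gives 351.)

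**Step 2: what the block 2 model estimates.** Let A be the group treated in year 1 and B the group treated in year 2.
- Difference at T2, B − A: −δ1.
- Difference at T3, B − A: δ2 − rδ1.
- ANCOVA of T3 on T2 and group: (δ2 − rδ1) − β(−δ1) = **δ2 + δ1(β − r)**.

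The bias δ1(β − r) is zero only if δ1 = 0 or r = β. It is positive when r < β and negative when r > β.

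**Step 3: size when intervention 2 does nothing** (δ1 = 0.3, δ2 = 0, n = 352). The apparent effect is 0.3(β − r). Rejection rates are from 2,000 simulated trials per cell.

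| β | r = 0 | r = 0.5 | r = 1 |
|---|---|---|---|
| 0.5 | +0.15 (37%) | 0.00 (5%) | −0.15 (37%) |
| 0.7 | +0.21 (78%) | +0.06 (12%) | −0.09 (21%) |
| 0.8 | +0.24 (97%) | +0.09 (29%) | −0.06 (15%) |

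Hand check at β = 0.7: the standard error is about √[(1 − 0.49) × 4/352] = 0.076. Then 0.21/0.076 ≈ 2.8, which corresponds to rejection in a little under 80% of trials. With δ1 = 0, simulated rejection was 6%, nominal within simulation error.

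**Step 4: size when intervention 2 truly adds 0.3.** At β = 0.7 the estimates are 0.51, 0.36 and 0.21 for r = 0, 0.5 and 1.

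**Step 5: maintenance.** Take δ1 = 0.3 as known from T2. The T3 difference, B − A, is δ2 − 0.3r:
- r = 0, δ2 = 0: 0 − 0 = 0.
- r = 0.5, δ2 = 0.15: 0.15 − 0.15 = 0.
- r = 1, δ2 = 0.30: 0.30 − 0.30 = 0.

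All three give the same T2-adjusted coefficient, 0 + 0.7 × 0.3 = +0.21 at β = 0.7. Complete fading with a null second intervention and complete retention with an equally effective one therefore look alike.

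**Step 6: T1 as covariate instead.** T1 precedes all treatment, so the coefficient becomes δ2 − rδ1. The βδ1 term goes, but the two blocks remain mixed: with δ2 = 0.3 and r = 1 the expected value is 0 although both interventions work.

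**The case against.** Several points on the other side stand.

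- **The bias is conditional.** It vanishes if block 1 has no effect, or if its gain persists at the same rate as other T2 differences (r = β), which is not absurd. At β = 0.5 with half the gain kept it is exactly zero. The high rejection rates require a programme worth 0.3 SD in year 1 and nothing in year 2. If both years have the same effect δ, the estimate is δ(1 + β − r), which cannot change sign for β ≥ 0 and r ≤ 1; the harm is then a mis-sized effect, not a false discovery.
- **Maintenance can be recovered under an assumption.** With equal effects in both years the T3 difference is δ(1 − r), and δ is known from T2. The article does not state that assumption.
- **Another analysis is planned.** The additional long-term ANCOVA shows that the T2-adjusted model is not the only use of T3. It is too unspecific to be a remedy, does not withdraw T2 as baseline, and cannot supply an untreated comparator.
- **The age of T2 is minor.** If year 2 follows the same second-half timetable, T2 is old by the time intervention 2 starts. That mainly costs precision and is not in itself a bias.

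A reader might also infer more than the article supports. It might seem that an arm difference of zero at T3 cannot be told from a programme that never worked; the T1-to-T2 comparison does separate those cases. It might seem that using T2 as covariate is what defeats the maintenance question; the cause is the role reversal, and T1 would not cure it. It might seem that block 2 is offered as a replication; the article never calls it that, gives access for every child as a reason for the crossover, calls maintenance an opportunity, and makes the direct comparison optional.

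**Conclusion.** The point holds in this form and should be fixed. The article commits itself to T2 as the block 2 baseline, and with role reversal and no new allocation this biases the estimate of intervention 2 by δ1(β − r). At the plan's own effect size and minimum sample, the error lies between −0.15 and +0.24 SD over β = 0.5 to 0.8 and r = 0 to 1, against a target of 0.3. β and r are assumed ranges. The rejection rates also assume independent children; clustering by class would change those rates but not the expected bias.

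Separately, between-arm T3 data cannot establish maintenance without assuming equal effects in both years. Neither problem touches the block 1 comparison of T2 adjusted for T1, so the trial's main efficacy question is not compromised by this point.

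**What to change.** 1. Name the T1-to-T2 comparison as the confirmatory efficacy test.
2. Analyse T3 with T1 as covariate and label the contrast *early versus delayed programme*. State that it estimates δ2 − rδ1, not the effect of intervention 2.
3. Present any T2-adjusted block 2 effect, the comparison of the two interventions and any maintenance statement as exploratory only. State the assumption each needs: r = β for the T2-adjusted effect, equal effects in both years for maintenance.
4. Report within-arm T2-to-T3 change descriptively, noting that it also contains maturation, schooling and test practice.

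The cost is rewording and one change of covariate, with no added data collection. The real price is that the block 2 efficacy and maintenance statements become weaker.

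### The optional repeated measures ANCOVA cannot compare the two interventions directly: once the groups swap roles, every candidate term needs an assumption about retention of the first-year effect

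*Protocol article*

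**What the plan says.** Section 2.4 (Procedure) sets out the design: "A crossover design will be used in which the role of each group is reversed during the following academic year". Of the second year it says: "In this block, the control and experimental groups will change roles". Children are assessed at T1 and T2 around the first intervention and at T3 after the second. The same section expects the second year to show whether the first group keeps its gains.

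Section 2.5 (Data Management and Analysis Plan) plans one ANCOVA per intervention. T1 is the baseline for the first. T2 is the outcome of the first and the baseline of the second. It then adds: "If desired, the effects of the two interventions can be directly compared by implementing a repeated measures ANCOVA". It does not say which outcomes enter that model, which covariate is used, whether the factor is group or condition, or which term is the comparison. It mentions neither the reversal of sign in year 2 nor retention. Later in the section, a further ANCOVA is planned for longer-term change at the end of the second block, allowing for change in the first.

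**The concern.** The question put to the model is whether d1 equals d2. In a parallel-group trial with repeated outcomes, an analyst would look at group-by-time. Here the treated group in year 1 is the control group in year 2, so the group contrast changes sign between blocks and the interaction adds the two effects instead of subtracting them. Any benefit that survives from year 1 also enters the T3 difference.

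At stake is a statement that delivery in the two years worked differently, or equally well, that would come from the role swap and from retention. The article also presents itself as a template for other research teams, so the sentence may be copied.

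**Working it through.** **Inputs from the protocol article.** Section 2.1.3 targets a Cohen's d of "0.3, which is a small-to-medium effect" and "indicated that the minimum sample size we require for the study is n = 352". It adds "we propose to recruit a total of 480 children", to allow for "slightly more than 25% of the sample to stop participation in the study". On allocation, section 2.4 says: "Efforts should be made to ensure as close to a 1:1 ratio of students between groups as possible".

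**Assumed, because not given.** Two-sided 5% level, 80% power for the sample size check, SD 1, correlation 0.6 between any two assessments, independent children, r from 0 to 1.

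**The plan's own figure.** A two-sample t calculation for d = 0.3 gives 176 per group, 352 in total, with power 80.1%. The stated minimum is reproduced. The dropout margin is (480 - 352)/480 = 26.7%, also as stated.

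**Expected contrasts.** Group A has the programme in year 1 and group B in year 2. Adjusted for T1, A minus B is:
- at T2: d1
- at T3: r*d1 - d2

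With T2 and T3 as repeated outcomes and T1 as covariate:
- group-by-time (T2 difference minus T3 difference) = (1-r)*d1 + d2
- group main effect (average of the two) = [(1+r)*d1 - d2]/2

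With each block's own baseline (T1, then T2):
- condition-by-block = (d1 - d2) + (r - slope)*d1, where slope is the within-group regression of T3 on T2 (0.6 under the assumption above)

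**Why no term escapes r.** There are two group differences and three unknowns. Take d1 = 0.3 with d2 = 0.3 and r = 1, and then d1 = 0.3 with d2 = 0 and r = 0. Both give 0.3 at T2 and 0 at T3. In the first case the effects are equal and fully kept. In the second the second delivery did nothing and the first effect faded. The group differences are identical.

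**Rejection rates at n = 352, normal approximation.**

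Group-by-time: the variance of T3 - T2 is 2*(1 - 0.6) = 0.8, so SE = sqrt(0.8*4/352) = 0.095.
- r = 1: 0.30/0.095 gives z = 3.15, rejection 88%
- r = 0.5: 0.45/0.095 gives z = 4.72, over 99%
- r = 0: 0.60/0.095 gives z = 6.29, 100%

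Group main effect: the residual variance of the mean of T2 and T3 given T1 is (1 + 0.6)/2 - 0.6^2 = 0.44, so SE = sqrt(0.44*4/352) = 0.071. With d1 = d2 = 0.3 the expected value is 0.15*r.
- r = 1: z = 2.12, 56%
- r = 0.5: z = 1.06, about 18%
- r = 0: 5%

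Simulation agrees with these. The three terms under equal effects (d1 = d2 = 0.3), where a valid test would reject in 5%:

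| Term | r = 0 | r = 0.5 | r = 1 |
|---|---|---|---|
| Group-by-time, T1 covariate | 100% | over 99% | 88% |
| Group main effect, T1 covariate | 5% | 18% | 56% |
| Condition-by-block, own baselines (simulated) | 39% | 7% | 21% |

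With d1 = d2 = 0 all three reject in about 5%, so the excess comes from testing a different hypothesis. Replacing the constant correlation by an autoregressive one leaves the pattern unchanged: group-by-time rejects in about 90% to 100%.

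**Missing a real difference.** With d1 = 0.3 and d2 = 0, group-by-time equals 0.3*(1-r). It rejects in 5% at r = 1, 12% at r = 0.75, about 36% at r = 0.5 and 88% at r = 0. In the same setting the main effect rejects in about 99% at r = 1. The main effect has its own blind spot where d2 = (1+r)*d1: with d1 = 0.3, d2 = 0.6 and r = 1 it is zero and rejects in about 5%.

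**The case against.** The strongest reply is that section 2.5 names no model terms, so the group-by-time layout is the critic's choice. The preceding sentence gives each intervention its own baseline, and the natural extension is a condition-by-block term. That term does target d1 - d2, and its false rejection rate is near nominal when r is about 0.5 to 0.6. A condensed article may leave the choice of contrast to a fuller document.

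Most of this stands. A reader might infer that the planned analysis is bound to report a false difference. The text does not support that, because it does not commit to group-by-time. A reader might also infer that a false difference becomes surer the longer the benefit lasts. That holds for the group main effect only; for group-by-time, false rejection falls from 100% to 88% as r goes from 0 to 1. Nor does group-by-time generally miss a real difference: that needs near-full retention and a small d2.

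The reply does not rescue the sentence. It asserts that the model makes a direct comparison, which goes further than leaving a detail open. Even the most favourable reading depends on r matching the within-group slope, and section 2.4 treats maintenance as something still to be found out.

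It is also fair that the analysis is optional, that the stated objectives pose no question about year of delivery, and that a separate longer-term ANCOVA is planned.

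**Conclusion.** The concern holds in a limited form. The design does not identify d1 - d2 without an assumption about retention, so the claim of a direct comparison is wrong under each of the three readings examined. Group-by-time is the worst of them, the group main effect is valid only with no retention, and condition-by-block is valid only with retention close to the within-group slope.

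The expected values follow from the role swap alone. The percentages rest on the assumed correlation, the chosen values of r and independent children. Whole classes are assigned, so they illustrate the size of the problem and are not this trial's actual error rates.

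The weight is minor. The analysis is offered only if wanted, and neither the ANCOVA for each intervention nor the figure of 352 depends on it.

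**What to change.** Remove the sentence in section 2.5, or qualify it as follows:
- State that group-by-time is not the comparison of the two effects, because the groups change roles.
- Report two group differences adjusted for T1, each with a confidence interval: T2 (programme against usual activity) and T3 (programme in year 1 against programme in year 2).
- If d1 - d2 is still wanted, name the contrast: either condition-by-block with each block's own baseline, or (1-r)*d1 plus the T3 difference. State its retention assumption and show the result over r from 0 to 1. For example, a T2 difference of 0.3 and a T3 difference of 0 give d1 - d2 anywhere from 0.3 (r = 0) to 0 (r = 1).
- Say that the design cannot separate a different second-year effect from fading of the first.

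The cost is wording and a few lines of analysis code, with no new data. The drawback is that the comparison becomes a range that depends on an assumption, in place of a single p-value.
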